## Abstract

**Introduction:**

A functioning voice is essential for normal human communication. A good voice requires two moving vocal folds; if one fold is paralysed (unilateral vocal fold paralysis (UVFP)) people suffer from a breathy, weak voice that tires easily and is unable to function normally. UVFP can also result in choking and breathlessness. Current treatment for adults with UVFP is speech therapy to stimulate recovery of vocal fold (VF) motion or function and/or injection of the paralysed VF with a material to move it into a more favourable position for the functioning VF to close against. When these therapies are unsuccessful, or only provide temporary relief, surgery is offered. Two available surgical techniques are: (1) surgical medialisation; placing an implant near the paralysed VF to move it to the middle (thyroplasty) and/or repositioning the cartilage (arytenoid adduction) or (2) restoring the nerve supply to the VF (laryngeal reinnervation). Currently there is limited evidence to determine which surgery should be offered to adults with UVFP.

**Methods and analysis:**

A feasibility study to test the practicality of running a multicentre, randomised clinical trial of surgery for UVFP, including: (1) a qualitative study to understand the recruitment process and how it operates in clinical centres and (2) a small randomised trial of 30 participants recruited at 3 UK sites comparing non-selective laryngeal reinnervation to type I thyroplasty. Participants will be followed up for 12 months. The primary outcome focuses on recruitment and retention, with secondary outcomes covering voice, swallowing and quality of life.

**Ethics and dissemination:**

Ethical approval was received from National Research Ethics Service—Committee Bromley (reference 11/LO/0583). In addition to dissemination of results through presentation and publication of peer-reviewed articles, results will be shared with key clinician and patient groups required to develop the future large-scale randomised controlled trial.

**Trial registration number:**

ISRCTN90201732; 16 December 2015.

Strengths and limitations of this studyThis is the first clinical trial to be run in the UK to compare the effectiveness of two surgical approaches for restoration of laryngeal function in adults with unilateral vocal fold paralysis (UVFP).This study has been developed in response to: (1) patient demand and (2) a systematic review that reported a low quality of current literature available on laryngeal reinnervation and proposed that a formal prospective trial was required using standardised, internationally accepted outcomes.A similar trial, comparing laryngeal reinnervation and type I thyroplasty in adults with UVFP, was previously run in the USA, but was suspended prematurely due to irregularity in obtaining inform consent and low accrual. We acknowledge the challenges associated with recruiting to a phase III surgical study of this type and have sought to overcome them by: (1) learning from this previous trial; (2) designing this rigorous feasibility study to be conducted prior to running a larger scale phase III randomised controlled trial and (3) involving patients with UVFP throughout the feasibility study design, set up, analysis and dissemination processes.Our research team is multidisciplinary and our study design incorporates both qualitative and quantitative components.While our study focuses on voice-related criteria for inclusion, our design includes outcomes relating to both the voice and swallowing.Although participants and study personnel are not blinded to their allocated treatment group, the speech therapist and neurophysiologist outcome raters are blinded.Very few ear, nose and throat surgeons in the UK are trained to perform laryngeal reinnervation and so our study is limited to recruiting at those relevant UK sites.While we aim to follow-up all participants for 12 months, budget and time constraints may limit some of the latterly recruited participant follow-up to 6 months. However, all patients are followed up clinically in the long term.

## Introduction

The larynx provides the main tool for human social interaction. The vocal folds are innervated by the recurrent laryngeal nerve (RLN) and when this nerve supply to one vocal fold is interrupted, unilateral vocal fold paralysis (UVFP) ensues. Patients suffering with UVFP typically display a weak, hoarse voice^1^ that tires easily, with some also suffering from breathing and swallowing problems. Quality of life of these patients is significantly reduced, with UVFP affecting their ability to interact socially and perform job functions.^2 3^Therefore, optimum restoration of the paralysed larynx is important for patients to lead full personal and professional lives.

The aim of treatment for UVFP is to achieve optimum vocal fold (VF) closure for voice production. Where speech therapy alone does not improve the voice sufficiently, surgical treatment is undertaken. While short-term relief of symptoms can be achieved via injection of the paralysed VF with a material to improve its position for the functioning VF to close against it, permanent results are only possible by two types of operation: surgical medialisation and laryngeal reinnervation. One method of the former is to insert a synthetic implant to move the paralysed VF into a better position for speaking (type1 thyroplasty), while the latter resupplies nerves to improve muscle bulk and tone (non-selective laryngeal reinnervation). Type I thyroplasty is a 1-hour operation under local anaesthetic where the medium grade silastic implant is inserted through a window in the cartilage lamina of the larynx. This implant medialises the paralysed VF in the midline position enabling the normal opposite vocal fold to make a firmer contact, producing a stronger voice. However, voice improvement may be short-term due to progressive atrophy of the denervated laryngeal muscles.^4^ Furthermore, this procedure does not restore vocal fold tension, meaning that pitch variation remains suboptimal.^5 6^ Reports on short and long-term voice outcomes of patients with thyroplasty are sparse and methodologically poor.^7^ The newer approach to restoring laryngeal function in UVFP patients, non-selective laryngeal reinnervation, is a 2-hour operation under general anaesthesia in which the injured RLN and the donor nerve are identified and anastomosed. Its aim is to restore innervation to the larynx by ‘borrowing’ the activity of other motor nerves, specifically the ansa cervicalis. As such it may re-establish the tone and bulk of the vocal folds during speech and re-enable pitch control, resulting in normal or sufficient voice. The operation is safe and results in sustained improvement of glottal closure, maintenance of the vocal fold edge and significant improvements in voice quality have been reported.^8^

A systematic review of studies on laryngeal reinnervation revealed that the quality of current literature is low and a formal prospective trial was recommended using standardised, internationally accepted outcomes.^9^ Before embarking on a trial that will use public resources and the time of patients and healthcare staff, we need to confirm that running a trial is feasible and that the chosen outcome measures truly reflect voice quality and patients’ perceptions.^10 11^ For these reasons, and others given above, a feasibility study is critical prior to designing, with patients, a multicentre, phase III randomised clinical trial of treatment for this disabling condition.

## Methods and analysis

### Objectives

The primary research objective is to determine the feasibility of performing a multicentre phase III randomised controlled trial (RCT) of laryngeal reinnervation versus type I thyroplasty for adult patients with UVFP.

The secondary research objectives are to test the feasibility of:The multicentre recruitment process, including continuous improvement to the process based on qualitative methodology;Recruiters being able to present true equipoise with the treatment arms;The randomisation processes and to investigate reasons for any difficulties that affect recruitment;The use of the following characteristics of the proposed primary and secondary outcomes: variability across patients, variability over time, differences in outcome between randomised groups over time;Process of follow-up visits;Means of gathering health economics and health-related quality of life data suitable for measuring cost-effectiveness.

### Study design

The feasibility study will consist of two research approaches run in parallel:Qualitative: the Quintet Recruitment Intervention (QRI) to understand the recruitment process and how it operates in clinical centres, so that sources of recruitment difficulties can be identified and suggestions made to change aspects of design, conduct, organisation or training that could then lead to improvements in recruitment^12^;Quantitative: a small randomised surgical trial of 30 patients to compare non-selective laryngeal reinnervation to type I thyroplasty. Patients will be randomised in a 1:1 ratio.

The study is single blinded whereby the raters of the secondary quantitative outcome of acoustic measures will be blinded to the time-point of the data recordings (preoperative or postoperative) and blinded to surgical intervention (laryngeal reinnervation or type I thyroplasty).

### Participants

#### Inclusion criteria

UVFP due to unilateral recurrent laryngeal nerve paralysis of traumatic, iatrogenic or idiopathic origin of between 6 and 60 months duration or symptoms that have not sufficiently improved with speech therapy alone, as determined by the patient and agreed by a multidisciplinary clinical team, after 6 months and pending a surgical decision;Age from 18 to 70 years old;Male or female;Able to provide informed consent;A significant voice disorder as measured by perceptual rating (GRBAS (grade, roughness, breathiness, asthenia, strain) Grade≥2)^13^ and Voice Handicap Index (VHI-10 score >16)^14^;Common laryngeal electromyography (LEMG, neurophysiological) criteria (Koufman Grades 2–5)^15^ in either the thyroarytenoid or posterior cricoarytenoid muscle on the paralysed side.

#### Exclusion criteria

Impaired vocal fold mobility but a normal EMG (Koufman Grade I);Severe lung disorders;Structural vocal fold lesions such as polyp;Previous laryngeal framework surgery;Cricoarytenoid joint fixation;Significant non-laryngeal speech abnormality (severe dysarthria determined by a panel of trained speech therapists);Previous level 2, 3 or 4 thyroid neck dissection;Previous ipsilateral surgical neck dissection;Previous radiotherapy to the head and neck;Laryngeal injection of a rapidly absorbable material in the last 6 months;Previous laryngeal injection of a non-rapidly absorbable material (eg, bioplastics, voice examiner);Neuromuscular disease affecting the larynx or multiple cranial nerve palsies.

### Setting

The study is sponsored by University College London Hospitals National Health Service (NHS) Foundation Trust. Potential participants will be recruited from three UK hospitals; the Royal National Throat, Nose and Ear Hospital (University College London Hospitals NHS Foundation Trust), Manchester Royal Infirmary (Central Manchester University Hospitals NHS Foundation Trust) and Poole Hospital (Poole Hospital NHS Foundation Trust). The study is run through the University College London evidENT team, with qualitative data analysed by the University of Bristol and quantitative data analysed by University College London and Australian Catholic University.

### Interventions

Laryngeal reinnervation: the surgical technique is an unselective reinnervation^16^ that aims to improve the muscle tone and bulk. Performed under general anaesthesia, the injured RLN and the donor nerve are identified and anastomosed.

Type 1 thyroplasty: this medialisation/augmentation technique is a static technique,^17^ performed under local anaesthesia that aims to improve the positioning of the paralysed vocal fold. It uses a medium grade silastic implant, cut by the surgeon into the correct size for the patient. This size is determined intraoperatively by using a measuring device while listening and visualising the larynx with flexible fibreoptic scope simultaneously. Concurrent arytenoid adduction is permitted to be performed in cases where there is a significant posterior gap that cannot be approximated with the silicon block alone.

### Outcome measures

The primary outcomes are from those patients who were eligible to enter the study:Whether the patient was randomised (yes/no);Whether the participant successfully received the allocated operation (yes/no);Whether the participant completed the trial (yes/no).

The quantitative secondary outcomes are:General health status measured using the validated EuroQoL 5 Dimensions 5 Levels^18^ questionnaire. Participants will self-administer the questionnaires at baseline, 6 and 12 months.Voice-related quality of life measured using the validated VHI-10.^14^ Participants will self-administer the questionnaires at baseline, 6 and 12 months.Swallowing-related quality of life measured using the validated Eating Assessment Tool (EAT-10.^19^ Participants will self-administer the questionnaires at baseline, 6 and 12 months.Vocal fold vibration measured detected using laryngeal videostroboscopy and graded using the Stroboscopy Research Instrument scale.^20^ Data will be collected at baseline, 6 and 12 months, anonymised and analysed by three independent trained raters.Perceptual voice quality measured using the GRBAS^13^ four-point grading scale (0—normal or absence of deviance; 1—slight deviance; 2—moderate deviance and 3—severe deviance) to evaluate ‘G’; the grade of the overall voice quality, ‘R’; roughness or harshness, ‘B’; breathiness, ‘A’; asthenia and ‘S’; strain. Voice recordings will be collected at baseline, 6 months and 12 months, anonymised and graded by three independent experienced speech therapists trained to enhance the intra-rater and inter-rater agreement.^21^
Acoustic voice quality of the participants’ voice recording will be captured and measured using the ‘On person Rapid Voice Examiner’,^22^ a specially designed portable voice analysis application that will be loaded onto Apple iPod Touch devices at each recruitment site. The noise-to-harmonic ratio, harmonic-to-noise, jitter, shimmer, shimmer dB, fundamental frequency, pitch range and maximum phonation time (MPT) data will be collected at baseline, 6 months and 12 months.Swallow volume, capacity and speed measured using the validated 100 mL water Swallow Test^20^ at baseline, 6 months and 12 months.Laryngeal muscle activity detected using LEMG and graded using the Koufman grading scale.^15^ Data obtained will be collected at baseline and 12 months, anonymised and analysed by three independent neurophysiologists.Health economic cost analysis of laryngeal reinnervation and thyroplasty procedures including the costs of the index procedure (staff costs, theatre costs, costs of consumables, recovery costs).Feasibility assessment of conducting a full economic evaluation of laryngeal reinnervation versus thyroplasty alongside the future large-scale RCT. Data will be collected to identify: (1) the main NHS/Personal Social Services cost components; (2) the main costs borne by patients and families and (3) the resource use and unit cost data required for each of these cost components and how best to source these.

The qualitative secondary outcomes are:Whether members of the Study Management Group (SMG) and recruiters are in equipoise with the treatment arms;Patient views and beliefs on randomisation, recruitment and retention processes;Patient and surgeon/speech therapist views on chosen outcome measures;Recruiter–patient interactions.

### Sample size

The sample size of 30 participants (15 per arm) will allow us to demonstrate the feasibility of conducting a full-scale randomised trial in the future. This study is not formally powered to detect differences (although we note that the sample would be able to detect very large effects, for example, a standardised effect of 1 with approximately 80% power). Rather, the sample size was based on Julious^20^ who suggests a group size of at least 12 to obtain reasonably precise estimates of an effect and its variance.

### Participant flow

During the 15-month recruitment period, potential participants will attend an initial ear, nose and throat (ENT consultation with the local principal investigator (PI). If they are deemed a potential candidate for the study, the PI will ask the patient for verbal consent to audiorecord subsequent conversations where information about the VOCALIST study is given. The PI will then provide the participant information sheet (PIS). After the consultation, the local research nurse (RN) will go through the PIS with the patient and answer any questions the patient may have. This conversation will also be audiorecorded and during this conversation the RN will ask the patient to complete written informed preconsent for the conversations to be audiorecorded and analysed by the qualitative research team.

If the patient is willing to participate in the study, the RN will arrange to call the patient within 1–3 days to book a date for the screening appointment. During the telephone call (also audiorecorded) the RN will answer any further patient questions and give the patient the opportunity to change their mind about study participation if they wish. If the patient confirms they would like to participate, the RN will book the patient’s screening appointment at their local site.

At the screening and baseline appointments, informed consent will be obtained by the RN prior to the assessments being performed. Throughout the recruitment process the RN will remind patients that they are under no obligation to enter the study and that they can withdraw at any time, without having to give a reason. No clinical trial procedures will be conducted prior to taking consent from the participant. Consent will not denote enrolment into trial. Figure 1 shows the flow of patients through the study and the assessments performed at each visit.

**Figure 1 F1:**
[figure not shown]
Flow diagram of the VOCALIST feasibility study. EAT-10, Eating Assessment Tool 10-items; ENT, ear, nose and throat; EQ-5D-5L; EuroQoL 5 Dimensions 5 Levels; LEMG, laryngeal electromyography; OperaVOX, On person Rapid Voice Examiner; VHI-10, Voice Handicap Index 10.

### Randomisation

Participants will be allocated to either of the two operations (see figure 1) using block randomisation stratified by centre to ensure that approximately equal numbers of patients are allocated to each treatment arm within each centre. The randomisation will be carried out using the web-based service from the company ‘Sealed Envelope’. Varying block sizes will be used and these will only be known to the statistician and Sealed Envelope.

### Data analysis plan

#### Quantitative data analysis

Descriptive analyses (means, SD and proportions) will be used to summarise the characteristics of the patients recruited to the study. A consort flow diagram will be produced to show the progress of the participants through the phases of the feasibility study and describe the follow-up at the various time-points. The study dataset will be analysed on an intention-to-treat basis. The primary and secondary outcomes will be analysed descriptively (using either proportions, or means, as appropriate) for each group. Differences between groups will be estimated and presented with 95% CIs. No formal comparisons will be made as the study is not powered for this. Stata V.14 will be used for analysis.

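### Group differences in the continuous secondary outcomes are most plainly read as unadjusted; using baseline and centre would probably sharpen them, and reporting the within-patient correlation would serve a stated objective

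*Protocol article*

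**What the plan says.** The Quantitative data analysis section gives the method in two sentences. The first is "The primary and secondary outcomes will be analysed descriptively (using either proportions, or means, as appropriate) for each group". The second is "Differences between groups will be estimated and presented with 95% CIs". No formal comparisons are to be made. No covariate, model or stratification term is named. SDs are mentioned for patient characteristics but not for outcomes.

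Three other sections bear on this:

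- Outcome measures: EQ-5D-5L, VHI-10, EAT-10, the acoustic measures and the water swallow test are all recorded at baseline, 6 and 12 months.
- Randomisation: allocation is made "using block randomisation stratified by centre", across three hospitals.
- Objectives: the characteristics of the proposed outcomes to be studied are "variability across patients, variability over time, differences in outcome between randomised groups over time".

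The Sample size section justifies 15 per arm by precision, citing guidance that calls for "a group size of at least 12 to obtain reasonably precise estimates of an effect and its variance".

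**The concern.** The study's stated reason for its size is a reasonably precise estimate of an effect and its variance. For the clinical outcomes, that precision depends on the estimator as well as on the number of patients. A simple difference of follow-up means leaves out the baseline measurement of the same quantity, and it leaves out the stratification factor. At 15 per arm, any chance difference between the arms at baseline carries through to the follow-up difference in proportion to the baseline slope.

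There is also a gap between objective and output. Means, proportions and differences address differences between groups over time. The raw SD at each visit can be worked back from a CI, so variability across patients is also within reach. Variability over time is different: the correlation between visits cannot be recovered from separate summaries at each visit. Anyone planning the phase III trial with a baseline-adjusted analysis would need the SD together with that correlation, and this study is the natural place to estimate it.

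**Working it through.** **Inputs.** 30 participants, 15 per arm, and a standardised effect of 1 (Sample size); 1:1 allocation (Study design); three centres (Setting). The significance level is not stated, so two-sided 5% is assumed, in line with the 95% CIs. The correlation r between baseline and follow-up is not given, so a range is used. All half-widths are in units of the outcome SD.

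**The plan's own figure.** The article claims "a standardised effect of 1 with approximately 80% power". By the normal approximation, 1/√(2/15) = 2.739 and 2.739 − 1.960 = 0.779, which gives power of 78.2%. This agrees with the stated figure. The exact two-sample t calculation gives 75.3%.

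**Unadjusted half-width.** t(0.975, 28) × √(2/15) = 2.048 × 0.365 = 0.748.

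**Adjusted half-width.** ANCOVA with baseline and two centre terms has 30 − 5 = 25 degrees of freedom. The half-width is t(0.975, 25) × √(2/15) × √(1 − r²) × √(1 + 1/26). The last factor, 1.019, is the average cost of chance baseline imbalance. Centre is assumed to explain nothing, so all the gain shown comes from baseline.

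| r | Before imbalance factor | With imbalance factor | Change from 0.748 |
|---|---|---|---|
| 0 | 0.752 | 0.766 | +2.5% |
| 0.2 | 0.737 | 0.751 | +0.4% |
| 0.3 | 0.717 | 0.731 | −2% |
| 0.5 | 0.651 | 0.664 | −11% |
| 0.7 | 0.537 | 0.547 | −27% |

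With 12 per arm, as after some loss to follow-up, the unadjusted half-width is 0.847. The changes at r = 0.3, 0.5 and 0.7 are then about −1%, −10% and −26%.

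**Chance imbalance.** The SE of the baseline difference is √(2/15) = 0.365 SD. A difference beyond 0.5 SD in either direction lies 0.5/0.365 = 1.37 SEs out, which has probability 17%. An imbalance of 0.5 SD moves the unadjusted difference by 0.5 × 0.5 = 0.25 SD if the baseline slope is 0.5, and by 0.15 SD if it is 0.3.

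**What r is worth for planning.** As an illustration, assume an effect of 0.5 SD, 80% power and two-sided 5%. The raw SD gives 2 × (1.960 + 0.842)²/0.5² = 62.8, so 63 per arm. Multiplying by 1 − r² (0.91, 0.75 and 0.51) gives 58, 48 and 33 per arm at r = 0.3, 0.5 and 0.7.

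**The case against.** The strongest reply is that the point leans on silence in a condensed article. The section names no estimator, does not call the differences unadjusted and does not exclude adjustment. Covariates are commonly left to an analysis plan, and any such plan is not shown. A reader might infer that the sponsor has decided against using baseline and centre; the text does not support that. What stands is narrower. A method is stated, its plainest reading is a simple difference, and its listed outputs do not reach one part of a stated objective.

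A reader might also infer that the phase III variance will be wrong. It will not: the raw SD is valid and, if the later trial adjusts, conservative. An estimate of r from about 30 patients is itself imprecise. At an observed 0.5, Fisher's transformation gives 0.549 ± 1.96/√27, or 0.17 to 0.73 on the correlation scale. Planning on a residual SD alone could leave the next trial underpowered. That is why r should be reported with a CI and the raw SD kept alongside.

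Nor can the CIs be called needlessly wide as a matter of fact, because that depends on r. The entry thresholds on VHI-10 and GRBAS grade restrict the baseline range and may lower r. At about 0.2 or below, adjustment gains nothing.

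Finally, chance imbalance under randomisation is not bias, and the unadjusted CI already allows for it. Leaving out centre after stratified allocation makes the CI conservative, if anything. The yes/no primary outcomes have no baseline value and no tests are planned, so the recruitment and retention findings are untouched. All of this stands and limits the weight of the point.

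**Conclusion.** The point holds as an improvement to the analysis of the continuous secondary outcomes, not as an error of validity. As written, the analysis is most plainly an unadjusted difference. It probably gives up precision that the trial's own rationale values: about 2%, 11% or 27% of the CI half-width at r of 0.3, 0.5 or 0.7, and nothing at about 0.2 or below. These figures assume 15 per arm with complete data, a linear baseline effect and no contribution from centre; r itself is an assumption. Separately from any gain in precision, the listed outputs include no within-patient correlation, which the objective on variability over time calls for and which the planned data can supply.

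**What to change.** State in the Quantitative data analysis section whether differences are adjusted. For the continuous secondary outcomes only:

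- Estimate the 6- and 12-month differences either by ANCOVA at each visit, with arm, baseline value and centre, or by one mixed model with arm, visit, arm-by-visit, baseline value and centre. Give 95% CIs and no p-values. The mixed model also uses the 6-month data of late recruits who, as the limitations list warns, may not reach 12 months.
- Report raw means and SDs by arm and visit alongside.
- Report the residual SD, and the correlations among baseline, 6 and 12 months with CIs.

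Ordinal gradings such as GRBAS and the binary primary outcomes stay with the descriptive analysis already planned.

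The cost is a few sentences of analysis text and a few lines of Stata, with no new data. Statistically, the ANCOVA spends about three degrees of freedom, and precision falls slightly (half-width up by about 2.5% at r = 0) if the correlation proves very low. If an analysis plan already specifies this adjustment, the article's wording only needs to be aligned with it.
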